**Fig. 1 Fig1:**
[figure not shown]
STRONG trial design

Each patient who has signed the Informed Consent Form is monitored for a period of 30 weeks (24-week treatment phase and 6-week safety follow-up) during which patients will attend nine visits (examination schedule in Table 1; see also Fig. 2. (Additional file 1). A computer-based centralised randomisation scheme for all study sites will employ a 1:1:1 treatment assignment ratio (main study) using block randomisation with sequential numbering for each specific trial site. Subjects, investigators, site personnel, monitoring staff, data management and other sponsor personnel, excluding the Clinical Supplies Unit, will be masked to subjects’ assignments. Only in the case of a serious adverse event (SAE), when the masked information is urgently needed for the treatment of the subject, will treatment allocation be revealed.

**Table 1 Tab1:** Examination schedule

Protocol activity	Screening	Baseline	Week 4	Week 8	Week 12	Week 16 + 20	Week 24/early termination	Week 30 (follow-up)
	V1	V2	V3	V4	V5	V6 + 7	V8	V9
Informed consent	X							
Demographic data (age, gender)	X							
Medical and ophthalmic history	X							
Concomitant medications and procedures	X	X	X	X	X	X	X	X
Adverse events	X	X	X	X	X	X	X	X
NEI-VFQ-25/EQ-5D/ Compliance questionnaires		X			X		X	
Vital signs (blood pressure/pulse)	X				X		X	
Electrocardiogram	X						X	
Haematology	X				X		X	
Blood chemistry	X				X		X	
Urinalysis	X				X		X	
Obtain blood sample for risk factor substudy	X							
Obtain blood sample for biomarker substudy	X				X		X	
Pregnancy test (urine or serum)^a^	X							
Physical exam	X							
Best-corrected visual acuity (BCVA) (ETDRS)	X	X	X	X	X	X	X	X
RAPD	X							
Slit lamp biomicroscopy	X	X	X	X	X	X	X	X
Goldmann perimetry/semi-automatic kinetic perimetry	X^d^							
Schirmer test II (biomarker substudy)	X				X		X	
Goldmann applanation tonometry (±1 h)	X^c^	X	X	X	X	X	X	X^c^
Gonioscopy (study eye only)	X	X	X	X	X	X	X	X
Anterior segment and gonioscopic photography^b^	X		X		X		X	
Posterior segment OCT (SD-OCT)	X		X	X	X	X	X	
Indirect ophthalmoscopy	X	X	X	X	X	X	X	X
Fundus photography^b^	X				X		X	
Fluorescein angiography^b^	X				X		X	
Review inclusion/exclusion criteria	X	X						
Randomisation		X						
Administer study treatment (aganirsen or placebo)		X						
Drug dispensing/return and bottle weight		X	X	X	X	X	X	
Patient diary dispensing/return		X	X	X	X	X	X	
Assess rescue treatment criteria			X	X	X	X	X	X

*BCVA* best-corrected visual acuity, *EDTRS* Early Treatment Diabetic Retinopathy Study, *EQ-5D* EuroQoL five dimensions questionnaire, *IEC*, *Independent Ethics Committee*, *IOP* intraocular pressure, *NEI*-*VFQ-25* National Eye Institute Visual Function questionnaire 25, *RAPD relative afferent pupillary defect*, *SD-OCT* spectral domain optical coherence tomography

^a^Pregnancy tests may also be repeated as per request of IECs or if required by local regulations. Only applicable for women of childbearing potential

^b^Optional at all other visits: only if neovascularisation is suspected in slit lamp examination, gonioscopy or indirect ophthalmoscopy

^c^IOP measurement by Goldmann applanation tonometry can be performed at any time of the day at the screening visit, V9 and at an unscheduled visit. The time (±1 h) of IOP measurement at the baseline visit is mandatory for all other visits (V3–V8)

^d^Perimetry can be skipped if eligibility is fulfilled by other criteria

**Fig. 2 Fig2:**
[figure not shown]
Standard Protocol Items: Recommendations for Interventional Trials (SPIRIT) figure

The two study groups will be treated with aganirsen ‘low-dose’ (43 μg per day) or ‘high-dose’ (86 μg per day). The control group will receive placebo, as there is no labelled treatment for iCRVO to prevent NVG. The placebo is optically identical to the aganirsen emulsion.

Images of the anterior segment and gonioscopic photos of all patients participating in the STRONG study will be collected and evaluated for neovascularisation within the imaging substudy. Tears and serum samples will be collected during the biomarker substudy from 200 patients to evaluate possible markers for both iCRVO and NVG. The results will be compared with results of healthy subjects already available in a German database. Thirty-three eligible patients will be included in the risk factor substudy across all participating trial sites. At UMC Mainz, 33 age- and gender-matched healthy controls will be recruited. Blood samples will be collected to analyse laboratory parameters for coagulation and fibrinolysis and genetic factors to identify risk factors for iCRVO.

Protocol assistance at the European Medicines Agency (EMA) has taken place to define patients with a high risk for developing NVG. The inclusion criteria must be fulfilled at both the screening and baseline visits.

### Inclusion criteria

Primary iCRVO or conversion to iCRVO for no longer than 4 weeks in the study eyeBest-corrected visual acuity (BCVA) ETDRS letter score <35 letters (<20/200 Snellen equivalent) in the study eyeAt least a 10-disc area of retinal capillary obliteration on fluorescein fundus angiography in the study eye (central fundus: macular area as defined by the optic disc and the arcades, an approximate 6000-μm circle around the fovea) and/or large, confluent retinal haemorrhages in the study eyeIOP in the study eye ≤21 mmHgMale or female adults ≥18 yearsFor men and women of childbearing potential, willingness to utilise adequate contraception and not become pregnant (or have their partner become pregnant) during the full course of the study. Adequate contraceptive measures include (oral) hormonal contraceptives (stable use for two or more cycles prior to screening) and other prescription pharmaceutical contraceptives, intrauterine device, bilateral tubal ligation, vasectomy, condom, or diaphragm plus contraceptive sponge, foam, or jellyWilling, committed and able to return for all clinic visits and complete all study-related procedures. A written informed consent must be provided before any study-related procedure can be performed

Additionally, at least four out of six criteria must be fulfilled:A relative afferent pupillary defect (with a normal fellow eye)At least ten cotton-wool spots in the study eyeVenous tortuosity in the study eyePeripheral visual field defects corresponding to ischaemia: dense scotomas in areas of capillary nonperfusion in the study eye. Patient cannot see the I-2e target and has a defective or absent I-4e isopter (Goldmann perimeter or semiautomatic kinetic methods (Humphrey or Octopus visual field analyser), targets I-2e, I-4e, V-4e)Engorged vessels on the iris and/or chamber angle in the study eyeDetectable anterior chamber flare in the study eye

### Exclusion criteria

Ocular conditions with a worse prognosis in the fellow eye than in the study eyePrimary or secondary glaucoma in the study eyeOcular anti-VEGF treatment:Any anti-VEGF ranibizumab or bevacizumab treatment in the study eye in the last 45 days before the screening visitAny anti-VEGF aflibercept treatment in the study eye in the last 90 days before the screening visitAnti-VEGF treatment in the fellow eye during the trial
Any prior or concomitant use of systemic anti-VEGF productsPrevious use of intraocular corticosteroids in the study eye at any time or use of periocular corticosteroids in the study eye within 90 days prior to the screening visitPrevious use of intraocular or periocular corticosteroids in the fellow eye within 90 days prior to the screening visitHistory of idiopathic or autoimmune uveitis in either eyePresence of anterior segment neovascularisation (neovascularisation of the angle (NVA) or neovascularisation of the iris (NVI)), neovascularisation of the disc (NVD) or neovascularisation elsewhere (NVE) in the study eyePrevious PRP in the study eye Previous cyclocryocoagulation in the study eye Pregnancy and lactation Any abnormality in the study eye preventing reliable applanation tonometry Intraocular surgery (other than intravitreal anti-VEGF treatment) or laser treatment in the study eye within the last 90 days before the screening visit Evidence at examination of infectious blepharitis, keratitis, scleritis, or conjunctivitis in either eye, or current treatment for serious systemic infection Any ocular disorders in the study eye that, in the opinion of the investigator, might confound the interpretation of the study results or any other reason that, in the opinion of the investigator, precludes the subject from participating in this study Inability to obtain fundus photographs or fluorescein angiograms of sufficient quality to be analysed Allergy to fluorescein History of hypersensitivity to the study drug or to any drug with a similar chemical structure or to any excipient present in the pharmaceutical form of the investigational medicinal products History of other disease, metabolic dysfunction, physical examination finding, or clinical laboratory finding giving reasonable suspicion of a disease or condition that, in the opinion of the investigator, contraindicates the use of an investigational drug, might affect interpretation of the results of the study, or renders the subject at high risk from treatment complications History of breast cancer Medical or psychological condition that would not permit completion of the trial or signing of an informed consent Participation in other clinical trials during the present clinical trial or within the last 4 weeks

For the risk factor substudy, biomarker and imaging substudy, the same inclusion and exclusion criteria must be met by the patients.

Additional exclusion criteria were defined for the eligibility of patients for the risk factor substudy: age 65 years or older, renal insufficiency and acute malignant or inflammatory reaction (systemic or local).

The co-primary efficacy endpoints combine a neovascularisation component: presence of anterior segment neovascularisation (NVI or NVA), NVD and/or NVE in the study eye requiring PRP rescue treatment or cryotherapy rescue treatment up to week 24 scored dichotomously (yes/no) and an IOP component: percentage change (≥20%) in IOP compared to baseline and >21 mmHg in the study eye scored ‘failure’, while otherwise ‘success’.

The secondary endpoints of the trial are the time of development of secondary NVG in the study eye up to week 24 (in case aganirsen does not totally inhibit but slows down the development of NVG); the time of development of anterior segment neovascularisation (NVI or NVA); NVD or NVE in the study eye requiring PRP or cryotherapy up to week 24; the development of changes in BCVA (ETDRS letter score) in the study eye up to week 24 (from baseline); the development of needed additional laser treatments and re-treatments in the study eye at up to week 24 including the intensity of the needed additional treatment; the development of changes in the size of retinal nonperfusion areas in the study eye up to week 24 in comparison with the baseline; the development of changes in the National Eye Institute Visual Function questionnaire 25 (NEI-VFQ-25) health questionnaire total score at week 24 in comparison with the baseline; the development of changes in the EuroQoL five dimensions questionnaire (EQ-5D) health questionnaire (validated questionnaires) score at week 24 in comparison with baseline; absolute change from baseline in central retinal thickness in the study eye, assessed by spectral domain optical coherence tomography (SD-OCT) at week 24; NVG classification at 24 weeks on a scale from 1 (non-NVG) to 6 (most advanced NVG) based on central reading of neovascularisation and incidence, causality and intensity of adverse events between the treatment arms.

All randomised subjects, regardless of treatment group, may receive rescue treatment (e.g. PRP, cryotherapy or other, as routinely performed at the clinical site) at any time during the trial if they progress to anterior segment neovascularisation (NVI or NVA), NVD, or clinically relevant NVE in the fundus. In this case, the primary endpoint is reached and the patient will not further receive study medication. Should a patient receive rescue treatment with intravitreal anti-VEGF (i.e. Lucentis®, Eylea®) because of macular oedema (individual decision of the investigator), the patient will not further receive the study drug, but will be followed up for safety reasons.

The clinical trial will be performed in consideration of the Declaration of Helsinki and the International Conference on Harmonisation – Good Clinical Practice (ICH-GCP). The protocol (Version No.:1.4/Date 7 Jan 2015 Final) is approved by the institutional Ethics Committee from the Landesärztekammer Rheinland-Pfalz, Germany, and by the French Ethics Committee. Ethics approval in other participating countries/sites will follow. Any protocol amendment will be approved by the Ethics Committees and will be distributed to all participating trial sites via the sponsor’s delegated clinical research organisation. Additionally, all necessary documents in the current version will be available on a password-protected website. Personal information of participants will be treated as confidential. Only anonymous data will be forwarded to the sponsor for scientific evaluation. Data entry and storage is performed via an electronic data capture (EDC) system, including plausibility checks.

### Statistics

Presentation of the sample size is based on both aganirsen doses combined demonstrating superiority placebo on the co-primary endpoints of neovascularisation and IOP at 24 weeks. Calculation of the sample size is based on the following: (1) An aganirsen to placebo ratio of 2:1, (2) Neovascularisation measured dichotomously (NVG = yes/NVG = no) with estimated disease rates in the population of 0.25 for aganirsen and 0.48 for placebo. Testing of neovascularisation will be done using the normal approximation to the chi-square distribution for consistency with O’Brien-Fleming Alpha spending, which is also computed based on normal approximation, (3) IOP measured dichotomously with estimated rates of events in the population of 0.24 for aganirsen and 0.41 for placebo at 24 weeks and (4) Up to four performed analyses. Based on albeit heterogeneous historical data, we estimate that 25% of subjects in the aganirsen group and 48% in the placebo group will develop NVG by 24 weeks. Given a 2:1 aganirsen to placebo assignment ratio, a total of 300 evaluable subjects – 200 with aganirsen and 100 with placebo – will provide 80% power to reject the null hypothesis that aganirsen is no better than placebo. Power computation is based on the chi-square test with a two-sided alpha = 0.05. Assuming that approximately 10% of subjects will not be evaluable due to loss to follow-up and other reasons, a total of 333 subjects are planned for this trial. Missing values of NVG and IOP will be imputed using the last observation carried forward (LOCF) method.

Primary efficacy will be assessed up to four times: two initial futility analyses, followed by an interim analysis for success/futility/continuation and a final analysis. The data will be summarised in tables listing the mean, standard deviation, minimum, median, maximum and number of subjects in a group for continuous data or in tables listing count and percentage for categorical data, where appropriate. Data listing by subject will be provided. The effects of noncompliance, dropouts and covariates, and their interactions with treatment will be assessed to determine the impact on the general applicability of results from this study. Secondary comparisons will be considered exploratory, so that there will be no Type I error adjustment for multiple secondary comparisons.

### Co-primary efficacy I: NVG

The primary efficacy analysis will compare the proportion of subjects who developed NVG in the combined aganirsen arms versus in the placebo group. The analysis will test the following hypotheses: H0: P(NVG)_aganirsen_ ≥ P(NVG)_placebo_ and H1: P(NVG)_aganirsen_ < P(NVG)_placebo_, where P(NVG) is the proportion of subjects developing NVG by 24 weeks. The hypotheses will be tested using chi-square normal approximation. (‘Yes’: development of NVI, NVA, NVD and/or NVE, or rescue treatment and ‘No’: otherwise).

### Co-primary efficacy II: IOP

H0: Proportion (IOP Failure)_aganirsen_ ≥ Proportion (IOP Failure)_placebo_ and H1: Proportion (IOP Failure)_aganirsen_ < Proportion (IOP Failure)_placebo_, where IOP Failure = increase in IOP from baseline to week 24 by ≥ 20% and IOP > 21 mmHg, or rescue treatment, and IOP success = otherwise.

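### The IOP co-primary has two conflicting definitions, and the one in the analysis section lets an effect on new vessels alone produce a significant IOP result

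*Protocol article*

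**What the plan says.** **IOP endpoint, first statement.** The paragraph on co-primary efficacy endpoints (Methods/design, after the exclusion criteria) describes "an IOP component: percentage change (≥20%) in IOP compared to baseline and >21 mmHg in the study eye", scored as failure, with everything else a success. Rescue does not appear in it.

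**IOP endpoint, second statement.** Under Co-primary efficacy II: IOP, failure is "increase in IOP from baseline to week 24 by ≥ 20% and IOP > 21 mmHg, or rescue treatment".

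**NV endpoint.** The endpoint paragraph counts new vessels "in the study eye requiring PRP rescue treatment or cryotherapy rescue treatment up to week 24". Under Co-primary efficacy I: NVG the event is "development of NVI, NVA, NVD and/or NVE, or rescue treatment", so vessels count there with or without rescue.

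**Rescue.** Patients who progress to new vessels "may receive rescue treatment (e.g. PRP, cryotherapy or other, as routinely performed at the clinical site) at any time during the trial"; the primary endpoint is then reached and study medication stops. The same paragraph also calls intravitreal anti-VEGF for macular oedema rescue treatment.

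**Planning.** The Statistics section gives NV rates of 0.25 (aganirsen) and 0.48 (placebo), and "IOP measured dichotomously with estimated rates of events in the population of 0.24 for aganirsen and 0.41 for placebo at 24 weeks". It plans 200 v 100 evaluable patients for 80% power. The final two-sided alpha is 0.04288.

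**The concern.** A patient rescued for new vessels with normal pressure is an IOP success under one statement and an IOP failure under the other. Both rules are printed for the same co-primary endpoint, so this is not a detail left to an analysis plan.

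The choice changes what the trial can show. The Background says the trial will evaluate both the appearance of neovascularisation and the rise in IOP. If rescue fails a patient on both endpoints, and rescue is triggered mainly by vessels, the second test is in part a repeat of the first. A drug that reduces rescued neovascularisation and leaves pressure untouched could then be reported as having met the IOP endpoint.

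The planned IOP rates are also lower than the planned NV rates in both arms. That is natural for a pressure-only endpoint, but hard to square with one that also includes every rescue.

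**Working it through.** **1. The plan's own sample size.** Inputs: IOP rates 0.41 v 0.24, 2:1 allocation, two-sided alpha 0.04288 (z = 2.025), 80% power (z = 0.842). The pooled rate is (0.41 + 2 × 0.24)/3 = 0.2967.

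- Uncorrected placebo n = [2.025 × √(1.5 × 0.2967 × 0.7033) + 0.842 × √(0.41 × 0.59 + 0.24 × 0.76/2)]² / 0.17² = 90.7, so 91.
- With continuity correction: (90.7/4) × [1 + √(1 + 6/(2 × 90.7 × 0.17))]² = 99.3, so 100 placebo and 300 in total.

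This matches the plan's 300. The NV rates need only 150 to 177, depending on alpha (0.05 or 0.04288) and correction. The IOP rates therefore drive the sample size.

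**2. Power at 200 v 100, alpha 0.04288, no correction, final analysis only.** Power = Φ[(d − 2.025 × s0)/s1], where s0 and s1 are the standard errors under the null and the alternative.

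- IOP: Φ[(0.17 − 2.025 × 0.0559)/0.0577] = Φ(0.983) = 83.7%.
- NV: Φ[(0.23 − 2.025 × 0.0574)/0.0586] = Φ(1.940) = 97.4%.
- Both, if independent: 0.974 × 0.837 = 81.5%.

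**3. Do the planned IOP rates fit the composite definition?** If every NV case were rescued, composite IOP failure would be at least 0.25 (aganirsen) and 0.48 (placebo), and 0.24 and 0.41 could not occur. If some NV cases are not rescued, the rates can occur. They then require these minimum shares of NV cases to be neither rescued nor pressure failures:

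- aganirsen: (0.25 − 0.24)/0.25 = 4%
- placebo: (0.48 − 0.41)/0.48 = 14.6%

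At exactly these shares, no patient without NV could fail on pressure.

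**4. Chance of a significant IOP benefit when the drug has no effect on pressure.** Let s be the share of NV cases rescued and q the pressure-failure risk in all other patients, equal in both arms. The documents give neither. With rescue rate r = s × 0.48 (placebo) or s × 0.25 (aganirsen), composite IOP failure is r + (1 − r)q. Example with s = 1 and q = 0.10: placebo 0.48 + 0.52 × 0.10 = 0.532; aganirsen 0.25 + 0.75 × 0.10 = 0.325.

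| s | q | placebo | aganirsen | chance of significance |
|---|---|---|---|---|
| 1.00 | 0.05 | 0.506 | 0.288 | 95.3% |
| 1.00 | 0.10 | 0.532 | 0.325 | 92.4% |
| 1.00 | 0.15 | 0.558 | 0.363 | 88.7% |
| 1.00 | 0.30 | 0.636 | 0.475 | 73.3% |
| 0.85 | 0.10 | 0.467 | 0.291 | 83.4% |
| 0.70 | 0.10 | 0.402 | 0.258 | 70.1% |
| 0.50 | 0.10 | 0.316 | 0.213 | 47.5% |

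Under the pressure-only wording, the chance of a significant result favouring aganirsen is about 0.04288/2 = 2.1%.

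**The case against.** Four counter-arguments deserve weight.

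**The endpoints are not strictly nested.** A reader might infer that every NV event is a rescue and every rescue an IOP failure, so that the planning rates are impossible. That requires the NV definition from the endpoint paragraph, the IOP definition from the analysis section, and rescue actually given in every case. The analysis section also counts unrescued vessels, the rescue paragraph says patients may receive rescue, and requiring rescue is not the same as receiving it. With 70% of NV cases rescued and 10% background failure, the composite rates are 25.8% v 40.2%, close to the planned 24% v 41%. This objection stands: the rates are awkward under the composite, not impossible.

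**The win is not automatic.** A reader might infer that the IOP test is simply won on vessels. The table shows a probability that depends on two unknown quantities and can fall below one half. If anti-VEGF for oedema counts as rescue, the modelled rates shift again, and oedema rescue unaffected by treatment would dilute the contrast. This too stands, although the tabulated values are all far above 2%.

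**Power is not short.** The planning rates give 83.7% for IOP, and full rescue with background failure of 5% to 15% gives 89% to 95%. No loss of power is shown.

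**A composite is legitimate.** Scoring an event that ends study drug as failure is a recognised strategy. Pressure after rescue is also affected by the rescue, and the article explicitly promises follow-up only after anti-VEGF rescue. This stands against making pressure-only the mandatory primary. It does not excuse printing both definitions.

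**Conclusion.** Wrong as written: a co-primary endpoint has two incompatible definitions. This conclusion comes from the text alone and needs no assumption.

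The consequence for interpretation is conditional. With NV at the planned rates and no effect on pressure, the composite gives a significant IOP result with probability from 47.5% to 95% over the range tabulated, against about 2% for pressure alone. The range rests on the assumed rescued share and background failure rate, on equal background risk in both arms, and on rescue being given only for NV.

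The planning rates behind the 300 evaluable patients are coherent with the pressure-only wording. Under the composite they hold only if at least 4% and 14.6% of NV cases escape both rescue and pressure failure. The documents do not support the stronger claims of impossible rates, a certain win or an underpowered trial. The damage is to the meaning of the second co-primary: under the composite, a positive result would not by itself show that a pressure rise was prevented.

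**What to change.** 1. State one IOP-failure definition, identically in the endpoint paragraph and under Co-primary efficacy II: IOP.
2. Say whether anti-VEGF given for macular oedema counts as rescue treatment in the endpoint.
3. State the IOP planning rates and power for that definition.
4. If the composite is kept, report the pressure-only result and the counts of each component beside it, and make no claim of preventing pressure rise from the composite alone.
5. If pressure-only is chosen, use the scheduled tonometry, confirm that IOP is measured at and after rescue, and keep pressure or rescue as a sensitivity analysis.

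Either route needs a wording change and one power calculation, and the article says recruitment is not yet open. The pressure-only route has a further cost: pressure after rescue partly reflects the rescue. Table 1 labels the week 24 visit as also the early-termination visit, so later readings after rescue for neovascularisation may not exist unless the protocol provides for them; the gap would otherwise be filled by last observation carried forward.

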Currently, reduction of IOP remains the focus of all therapeutic approaches for the majority of glaucoma patients, including those with NVG. For NVG, however, IOP-lowering medications are moderately helpful because outflow is obstructed and the accompanying inflammation and proliferative stimulus lead to the very poor success rate of fistulating glaucoma surgery. Currently, the common therapy for neovascularisation is pan-retinal photocoagulation (PRP), although additional anti-VEGF intravitreal injections have become more and more common for the therapy of neovascularisation. Thermic laser coagulation of the retina by PRP is strongly advocated and practiced widely for the management of iCRVO if new vessels have already formed [10, 11]. However, no definite guidelines exist regarding the exact indication and timing of PRP. As an alternative method of selective retinal ablation, pan-retinal cryotherapy may be performed on the peripheral fundus if the ocular media are too hazy for laser application.

There is a clear need to widen the existing therapeutic options for the treatment of iCRVO to prevent neovascularisation and NVG, with a specific focus on noninvasive therapeutic options aimed at prevention or early management respectively of the neovascular component of iCRVO. Hence, it is expected that aganirsen will benefit patients with iCRVO by interfering at an early stage in the neovascularisation process. Understanding the natural course of NVG, including biomarker and risk factor analysis, will further support the evaluation of new diagnostic and therapeutic interventions. These results could help to make early NVG diagnosis independently of an increased IOP by analysis of body fluids.

The primary objective of this multicentre randomised controlled study is to assess the efficacy and safety of aganirsen relative to placebo in preventing NVG in patients with iCRVO. We will evaluate the appearance of neovascularisation and the rise in IOP after 24 weeks (co-primary endpoint). We hypothesise that each of the two tested aganirsen doses will be superior to the placebo in preventing NVG at week 24. This study will also evaluate the effective dose of aganirsen.

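### The IOP failure rule does not count IOP-lowering treatment given outside rescue, so an un-rescued pressure rise treated down by week 24 is scored a success

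*Protocol article*

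**What the plan says.** The section on co-primary efficacy II of the protocol article defines failure as an "increase in IOP from baseline to week 24 by" at least 20% together with an IOP above 21 mmHg, and then adds "or rescue treatment, and IOP success = otherwise". The rule is exhaustive, since every patient is either a failure or a success.

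The endpoint list that follows the exclusion criteria gives the same thresholds: "percentage change (≥20%) in IOP compared to baseline and >21 mmHg in the study eye scored ‘failure’, while otherwise ‘success". It attaches no week to the IOP component and mentions no treatment there. The neovascularisation component in the same sentence runs up to week 24.

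The rescue paragraph after that list says that patients "may receive rescue treatment (e.g. PRP, cryotherapy or other, as routinely performed at the clinical site") at any time "if they progress to anterior segment neovascularisation (NVI or NVA), NVD, or clinically relevant NVE in the fundus". It also uses the word rescue for intravitreal anti-VEGF given for macular oedema. Raised pressure is not a trigger, and IOP-lowering drops or surgery are not named.

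The Background says: "Currently, reduction of IOP remains the focus of all therapeutic approaches for the majority of glaucoma patients, including those with NVG". It adds: "For NVG, however, IOP-lowering medications are moderately helpful because outflow is obstructed". None of the listed exclusion criteria bars such treatment during the trial.

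Table 1 schedules Goldmann tonometry and "Concomitant medications and procedures" at every visit.

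**The concern.** Patients enter with IOP of 21 mmHg or less and without glaucoma in the study eye. A new rise that needs pressure-lowering treatment is therefore close to the event the trial aims to prevent. The written rule can place such a patient among the successes.

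For example, a patient with a baseline of 18 mmHg reads 22 mmHg at week 8. The rise is 4/18 = 22% and the reading is above 21, so both thresholds are met. Drops are started and week 24 reads 18 mmHg. The change is 0%, no rescue was given, and the patient is a success.

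If the same share of failures is masked in each arm, more patients move in the arm with more pressure rises, which the plan expects to be placebo, and the difference shrinks. IOP is also the endpoint with less power, so the loss falls where there is least margin.

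**Working it through.** **Which patients are affected**

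| Patient | Score under the written rule |
|---|---|
| Received rescue, any week-24 IOP | Failure |
| No rescue, week-24 IOP meets both thresholds | Failure |
| No rescue, raised earlier, controlled by IOP-lowering treatment at week 24 | Success |

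Only the third row is at issue. Readings before week 24 enter only through LOCF, when a later value is missing. Rescue is also permissive (patients may receive it), so a patient with new vessels and raised pressure who gets drops but no rescue is a neovascularisation event and can still be an IOP success.

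**Inputs (Statistics section and section on the normal approximation to the chi-square test)**
- IOP event rates: 0.41 placebo, 0.24 aganirsen.
- Neovascularisation rates: 0.48 and 0.25.
- 100 placebo and 200 aganirsen evaluable.
- Final two-sided alpha 0.04288, z = 2.025.

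**The plan's own figure**

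For 80% power with k = 2 and d = 0.17, the pooled rate is (0.41 + 2 × 0.24)/3 = 0.2967.

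n(placebo) = [2.025·√(0.2967 × 0.7033 × 1.5) + 0.842·√(0.41 × 0.59 + 0.24 × 0.76/2)]² / 0.17² = (1.133 + 0.486)² / 0.0289 ≈ 90.7, rounded up to 91.

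With continuity correction: (90.7/4)·[1 + √(1 + 3/(90.7 × 0.17))]² ≈ 99.3, rounded up to 100. The total is 300, as stated.

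**Baseline power, uncorrected normal approximation**

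Power = Φ[(d − z·s₀)/s₁], where s₀ is the pooled and s₁ the unpooled standard error.

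IOP: s₀ = √(0.2967 × 0.7033 × (1/100 + 1/200)) = 0.0559 and s₁ = √(0.41 × 0.59/100 + 0.24 × 0.76/200) = 0.0577. Power = Φ[(0.17 − 2.025 × 0.0559)/0.0577] = Φ(0.983) = 83.7%.

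Neovascularisation, same formula: 97.4%. IOP is the limiting endpoint.

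**Effect of masking**

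The article gives neither the un-rescued share u of IOP failures nor the controlled share c of those. Both are assumed. Each rate becomes p × (1 − u·c).

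| u | c placebo | c aganirsen | Placebo rate | Aganirsen rate | Difference | Power |
|---|---|---|---|---|---|---|
| – | 0 | 0 | 0.410 | 0.240 | 0.170 | 83.7% |
| 10% | 20% | 20% | 0.402 | 0.235 | 0.167 | 82.6% |
| 10% | 50% | 50% | 0.390 | 0.228 | 0.162 | 80.9% |
| 20% | 20% | 20% | 0.394 | 0.230 | 0.163 | 81.5% |
| 20% | 50% | 50% | 0.369 | 0.216 | 0.153 | 77.9% |
| 10% | 40% | 20% | 0.394 | 0.235 | 0.158 | 78.9% |
| 20% | 40% | 20% | 0.377 | 0.230 | 0.147 | 73.4% |

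**Would an any-visit rule be better?**

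Counting a single reading at any of V3–V8 adds five visits. If each has a spurious crossing probability q (assumed), the rates become 1 − (1 − p)(1 − q)⁵. At q = 1% they are 0.439 and 0.277, with power 78%. At q = 3% they are 0.493 and 0.347, with power 66%. The cost can equal or exceed the loss it would repair.

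**The case against.** The main disease path runs through rescue. The Background attributes the pressure rise to new vessels obstructing the trabecular meshwork. Table 1 schedules gonioscopy and a check of rescue criteria at each of V3–V8, and the list of rescue treatments is open-ended. Most neovascular pressure rises may therefore bring rescue and already count as failures. This stands, and it confines the gap to patients without rescue.

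A reader might infer that any patient treated down before week 24 becomes a success. The rescue clause in the same sentence rules that out.

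A reader might also apply the masking to all IOP failures. Masking 20%, 30% or 50% in both arms would give power of 71%, 64% or 47%. Masking 40% of placebo and 20% of aganirsen failures would give 18%. The arithmetic is right but the base is wrong, because rescued failures cannot turn into successes. The planning rates are also stated as rates at 24 weeks and may already reflect pressure treated by then, in which case even the smaller deduction counts some of it twice.

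A fixed-time reading for one co-primary beside a cumulative one for the other is a recognised choice and not an error in itself.

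The full protocol, which is not shown, may say more about concomitant IOP-lowering treatment. That would excuse silence. Here, however, the article states a complete rule whose remainder category takes these patients in.

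**Conclusion.** The point holds in a limited form. The written IOP rule classes as successes those patients without rescue whose pressure rise is controlled at week 24 by newly started IOP-lowering treatment. The direction is dilution of the limiting co-primary. On the assumed shares the loss is about 1 to 6 percentage points of power with equal masking, and about 5 to 10 points with the differential case. These figures rest on assumed un-rescued and controlled shares, on the planning rates being free of such masking, and on the uncorrected normal approximation at the final alpha. The documents do not support a claim of a large loss of power. The definition is worth correcting because the misclassification follows from the rule as written and the correction is cheap.

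**What to change.** In both the endpoint list and the co-primary efficacy II section, state week 24 as the time point of the IOP criterion. In both, add to the failure definition: or IOP-lowering medication or pressure-lowering surgery newly started in the study eye for raised IOP up to week 24. Keep the existing rescue clause. Take the information from the concomitant medication and procedure records in Table 1. Report the current rule and an any-visit (V3–V8) reading as sensitivity analyses. Do not make the any-visit reading primary, since single readings may cross the threshold by chance.

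This alters endpoint scoring only and asks for no change in care or data collection. There are two costs. The planning rates of 0.24 and 0.41 must be checked against the revised definition. Starting treatment is also partly at the investigator's discretion, although double masking limits the bias that this could bring.
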